### **6.1.3 Other study parameters**

At the start of the study the following subject characteristics will be measured:

- sex
- age (years)

- weight (kg)
- height (m)
- time since stroke (weeks)
- affected side (left/right)
- stroke type (ischaemic or haemorrhagic)
- dominant side (left/right)
- proprioception and sensation disorders (Modified Nottingham Sensory Assessment, Lincoln et al. 1998)
- cognition (Mini-Mental State Examination, Folstein et al. 1975)
- communication level (spontane communicatie onderdeel, Utrecht Communicatie Onderzoek, Blauw and Koning, 1988)

The characteristics of the treatment of the individual subject will be measured using questionnaires for clinicians and subjects (see attachment 1):

- use of additional walking aids
- standing and walking
- falling
- medication (spasticity related)
- AFO use

Furthermore, a questionnaire will be used to assess pain of the feet/ankles and using the shoes and AFO (see attachment 2).

## **6.2 Randomisation, blinding and treatment allocation**

The assignment to the “early or “late” AFO group will be randomised using block randomisation with blocks of 4 subjects. An independent person will perform this randomisation using random numbers (Fisher). Unfortunately, blinding of the patients and/or assessors is not possible because it is not possible to mask whether or not someone is wearing an AFO.

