### 3. STUDY DESIGN

In this explorative study a randomised experimental longitudinal design will be used. The intervention concerns the timing of providing AFOs to acute stroke patients during the rehabilitation process. In two groups the effect of timing of providing AFOs will be compared: 1) providing an AFO within one week after admission in the rehabilitation centre ( $\pm$  2 weeks after stroke); and 2) providing an AFO 8 weeks later.

Acute stroke subjects with indication for using an AFO during rehabilitation will be included. To avoid differences in therapy treatment and intensity between subjects, only one rehabilitation centre will participate in this study; The Roessingh Rehabilitation Centre in Enschede. Patients will be included in the study as soon as possible after admission into the Roessingh. In daily practice, this is within approximately 14 days after stroke onset. Participating patients will be randomised into 2 groups. The first group will receive the AFO within one week after admission into the Roessingh (referred to as the “early” AFO group). Subjects in the “early” group can practise walking and transferring using the AFO all day long: during the physiotherapy sessions, during other therapy sessions and during the stay at the ward. The second group (referred to as the “late” AFO group) will receive the AFO 8 weeks later than the “early” AFO group, approximately 10 weeks after stroke. In the period before receiving the AFO, this group will practise walking and transferring without support of the ankle and foot. If, during physiotherapy sessions, practising without support of the ankle appears to be impossible, bandaging of the ankle and foot is allowed, but only during the physiotherapy sessions. This bandaging is not continued during other therapy sessions, or during the stay at the ward.

The “late” AFO group will receive the AFO approximately 10 weeks after stroke. This period is chosen for 2 reasons. First, this is comparable to the period in which in clinical practice the final AFO is usually provided according to physiotherapists at the Roessingh (approximately 8-12 weeks after stroke). Second, prospective stroke studies indicate that the process of spontaneous recovery after stroke is almost completed after approximately 6-10 weeks (Buurke et al. 2008; Kwakkel et al. 2006).

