## 4. STUDY POPULATION

### 4.1 Population (base)

Acute stroke patients will be recruited from the Roessingh Rehabilitation Centre. Rehabilitation physicians from the Roessingh Rehabilitation Centre ( [REDACTED] ), all experienced in the management of stroke patients and previous involved in research projects, will carry out the first step in the subject recruitment. The rehabilitation physicians will select the subjects after admission into the Roessingh Rehabilitation Centre and ask them if they are interested in taking part in a research studying the effects of timing of providing an ankle-foot orthosis after stroke. If so, the physician will ask them if they give permission to pass on their names to the responsible researcher at the Roessingh Research and Development (RRD). The researcher will contact the patient and will provide him/her and his/her relatives, both verbally as well as written, with the necessary information about the study. In the information letter details about the purpose of the study and the measurements that will be performed are explained. All subjects are informed that they can stop with the measurements at any moment, without giving any reason and without experiencing any disadvantage.

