### 4.2 Inclusion criteria

- admission into the Roessingh Rehabilitation Centre
- unilateral ischaemic or haemorrhagic hemiparetic stroke (single and first ever or history of previous stroke with full physical recovery)
- time since stroke max 6 weeks
- age 18 years or older
- indication to use an AFO during rehabilitation because of:
  - problems with stability in stance
  - problems with footclearance during swing
  - problems with foot prepositioning in early stance
- no severe deficits in communication
- no severe deficits in memory and understanding

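### One printed block size of 4 in an open, single-centre trial makes about a third of allocations deducible and leaves room for selection bias

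*Protocol*

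**What the plan says.** Protocol 6.2 states that subjects are "randomised using block randomisation with blocks of 4 subjects". No second block size and no allocation ratio appear. On who does it, the section says "An independent person will perform this randomisation using random numbers". On masking, it says that "blinding of the patients and/or assessors is not possible because it is not possible to mask whether or not someone is wearing an AFO".

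Other sections set the conditions under which this sequence is used:

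- **One sequence.** Section 3 says that "only one rehabilitation centre will participate in this study" and that "Participating patients will be randomised into 2 groups". No stratification is stated, so all subjects come from one list.
- **Selection by the centre's own staff.** Section 4.1: "The rehabilitation physicians will select the subjects after admission into the Roessingh Rehabilitation Centre". Section 9.2 adds that these physicians make the first approach. A researcher then informs the patient, who has two days to decide.
- **Judgement in eligibility.** Section 4.2 requires an "indication to use an AFO during rehabilitation because of" any of three gait problems. Sections 4.2 and 4.3 also grade several deficits as severe without a cut-off.
- **Visible allocations.** Under Section 3 the early group has the AFO within a week of admission and may use it all day, including on the ward. The late group waits 8 weeks longer.
- **Accrual.** Section 4.4 expects about 20 subjects a year for 30 months, 50 in all.

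**The concern.** Blocking forces balance at known points, so past allocations carry information about the next one. With blocks of 4 the fourth place follows from the first three, and after two alike the third place follows as well. This does no harm if the people who choose patients cannot see past allocations or do not know the block size. Here the allocations can be seen at the centre and the block size is printed in the protocol.

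A recruiter who expects a given arm next could, knowingly or not, be more or less ready to find an AFO indicated in a patient with good or poor prospects. The arms would then differ at entry, and the outcomes are assessed openly as well. No analysis plan can make a predictable sequence unpredictable afterwards.

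**Working it through.** **The plan's own figure.** Accrual (4.4): 20 × 30/12 = 50 subjects, as stated. The protocol gives no figure for predictability.

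**Inputs.** Block size 4 and two arms (6.2); one list (3); N = 50 (4.4). The 1:1 ratio within blocks is an assumption. The observer is taken to know the block size and the order of past allocations.

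**Certain allocations, blocks of 4.** There are six equally likely sequences: EELL, LLEE, ELEL, ELLE, LEEL, LELE. The first two make places 3 and 4 certain; the other four make only place 4 certain.

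- Per block: (2 × 2 + 4 × 1)/6 = 4/3, and (4/3)/4 = 33.3%.
- At N = 50 (12 full blocks and 2 subjects): 12 × 4/3 = 16, and 16/50 = 32%.

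**Best guess, blocks of 4.** Always guess the arm with more places left.

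- Places 1 to 4 are guessed correctly with probability 1/2, 2/3, 2/3 and 1. The sum is 17/6 per block, and (17/6)/4 = 70.8%.
- At N = 50: 12 × 17/6 + 1/2 + 2/3 = 35.17, or 70.3%. Simple randomisation gives 50%.

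**Illustrative bias.** Let the enrolled patient's prognosis move by +d SD when one arm is expected, −d when the other is expected, and 0 at a tie. Each correct guess moves the difference in means by +d/25 (arms of about 25), and each wrong guess by −d/25. Ties cancel on average.

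- Net correct guesses: 2 × 35.17 − 50 = 20.33. Bias = 20.33 d/25 = 0.813 d, which is 0.20 SD for d = 0.25 and 0.41 SD for d = 0.5.
- The standard error of the difference is √(4/50) = 0.283 SD. The bias is then 0.72 or 1.44 standard errors, and a two-sided 5% normal test rejects in about 11% or 30% of trials. Simulation with a t-test gives 10% and 26 to 27%. It is lower mainly because the shifts also widen the spread within arms.

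**Big stick, maximum imbalance 3.** A fair coin is used unless the arms differ by 3.

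- Let q(k) be the chance that the arms differ by 2 after 2k subjects. Then q(0) = 0 and q(k+1) = 1/2 + q(k)/4, so q(k) = (2/3)(1 − 4^(−k)).
- From a difference of 2, one of the next two allocations is forced with probability 1/2. The expected number forced in 50 is the sum of q(k)/2 for k = 0 to 24, which is (25 − 4/3)/3 = 7.89, or 15.8%.
- Correct guesses: 7.89 + 42.11/2 = 28.94, or 57.9%.
- Bias: (2 × 28.94 − 50) d/25 = 0.316 d, which is 0.08 (0.16) SD.

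**Comparison at N = 50.** Mixed blocks are simulated; for certainty, the observer knows the set of sizes but not the block boundaries.

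| Rule | Certain | Guessed | Bias, d = 0.25 (0.5) | Type I error | Worst split |
|---|---|---|---|---|---|
| Fixed 4 | 32% | 70% | 0.20 (0.41) SD | 10% (27%) | 26 v 24 |
| Mixed 4/6/8 | about 2% | 68% | 0.17 (0.35) SD | 9% (20%) | 27 v 23 |
| Big stick, 3 | about 16% | 58% | 0.08–0.09 (0.16–0.17) SD | about 5% (7–8%) | 26 v 24 |

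Mixed blocks remove most of the certainty but little of the guessing advantage. Big stick does the reverse.

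**The case against.** A reader might infer that the physicians know one allocation in three. The protocol does not say that. They would need the block size, 1:1 blocks, the block boundaries and a complete ordered log, pooled over several physicians. Replacement of subjects withdrawn before using an AFO (6.5) could blur the count. This stands: allocations are deducible, not shown to be known.

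Physicians also do not enrol alone. The researcher informs the patient and the patient decides (4.1, 9.2). This limits steering but does not remove it, because the physicians still choose whom to put forward and nothing suggests that the researcher is unaware of past allocations.

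It is tempting to add that a patient could be held back for a few days to catch the wanted arm. The protocol's accrual makes that a weak route. One subject arrives every 365/20 = 18 days. If arrivals are Poisson, the chance that another patient takes the place is 1 − exp(−3/18.25) = 15% in three days and 24% in five. Section 3 also wants inclusion as soon as possible after admission. Judgement of eligibility is the route that remains.

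It would also go too far to say that nothing later could help. Section 6.1.3 records age, time since stroke, stroke type, sensation and cognition, so gross imbalance on these could be seen, and an analysis plan might adjust for them. Section 8.2 itself names only between-group tests, and unmeasured prognosis would stay uncorrected.

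Finally, the trial calls itself explorative, which lowers the stakes but does not justify keeping a weakness that is cheap to remove.

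**Conclusion.** The point holds as a weakness of design. Following 6.2 as written gives a sequence in which 32% of 50 allocations could be deduced and about 70% guessed. This rests on 1:1 blocks and an observer who knows the block size and follows past allocations. The independent person guards against sight of the list only.

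The documents do not show that selection bias will occur, and its size is unknown. The 0.20 (0.41) SD and 10% (27%) figures should be read as near-worst-case illustrations. They require every recruiter, for the whole inclusion period, to act on every guess in the same direction, with a two-way shift that puts 0.5 (1.0) SD between patients chosen for the two expected arms. No passage supports shifts of that size. The change should be made; confidence is medium.

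**What to change.** In 6.2, replace the fixed blocks of 4 with a statement that a less predictable restricted sequence is used, and give the allocation ratio. Keep the details of the restriction in a separate document held by the independent person and out of anything the recruiters use. Add that each allocation is released only after eligibility is recorded and consent is signed. The release step stops direct foreknowledge; the new and concealed restriction is what limits deduction.

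More than one sequence would do. Big stick with maximum imbalance 3 gives the lowest guess rate; randomly varied blocks of 4, 6 and 8 leave the fewest certain allocations.

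The cost is a short change to 6.2, notified to the METC under 10.2 if approval has already been given, and a new list. Balance suffers little. Fixed blocks already end at 26 v 24 in one third of trials, because 50 is not a multiple of 4. Big stick does so in about two thirds and never does worse; mixed blocks can reach 27 v 23. The timing of AFO provision is untouched.

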## **6.3 Study procedures**

The Modified Nottingham Sensory Assessment (proprioception and sensation), Mini-Mental State Examination (cognition) and the Utrecht Communicatie Onderzoek (communication level) are used to describe the subject population. These standard tests are performed once, in the first weeks after inclusion.

### Gait analysis

Gait analysis will be performed at the RRD. Both groups will be measured five times (see table 1):

- T1: The first measurement will be performed at the end of the first week of the study (T1). Subjects in the “early” AFO group receive their AFO at the beginning of this week and are measured with and without AFO. Subjects in the “late” AFO group will be measured without AFO.
- T9: The second gait analysis will be performed in week 9 of the study (T9). Subjects in the “early” group are now using the AFO for 8 weeks, subjects in the “late” group receive their AFO in this week. From now on both groups will be measured with and without using the AFO.
- T17: The third gait analysis will be performed in week 17 of the study (T17). Subjects in the “early” group are using their AFO for 16 weeks, subjects in the “late” group are using their AFO 8 weeks.
- T26: The fourth gait analysis will be performed in week 26 of the study, approximately 6 months after stroke.
- T52: The last measurement will be performed 1 year after stroke.

Measurements will be performed while walking at comfortable speed. If necessary, subjects can use walking aids (e.g. canes). The movements of the body while walking will be recorded with a VICON video based 3D kinematic measurement system (VICON-MX13+, Vicon Oxford Metrics, Oxford, UK), consisting of 6 infrared cameras, using passive reflexive markers. Subjects are asked to put on a short and top so the skin is suitable for proper marker placement. These markers will be attached to the subject on the feet, lateral malleolus, tibia, knee and femur of both legs, as well as on the pelvis. Vertical ground reaction forces will be measured with force plates, covered in the level walkway (AMTI-OR6-5, Advanced Medical Technologies, Inc, Massachusetts, USA). During the gait analysis muscle activity will be recorded using surface EMG from several superficial muscles of both legs using wet-gel silver/silver-chloride electrodes. Signals will be collected from the m. Rectus Femoris, m. Vastus Lateralis, m. Semitendinosus, m. Gastrocnemius and m. Tibialis Anterior. Electrode placement, skin preparation and related issues are performed according to the guidelines presented by SENIAM (Hermens et al. 1999).

### Clinical tests

All clinical tests and questionnaires measuring walking impairments, mobility, activities of daily life, falling and quality of life are performed according to the specific test protocols. During the first 18 weeks of the study most clinical tests will be repeated with 2-week intervals. Furthermore, the tests will be repeated 6 and 12 months after stroke (T26 and T52, respectively). All the clinical tests are performed with AFO.

The frequency of performing the various measurements is listed in Table 1.

Spasticity of the lower limb is assessed using the Mappam procedure. The subject is in a comfortable semi-reclined position (45°) with support for the back and lumbar region. Knee flexor and extensor muscles are recorded while performing the pendulum test (passive swing movement of the lower leg from full extension and then released), and during passive movement. The subject is instructed to relax his/her leg and not to oppose or facilitate the passive movements. The subject is asked to perform an active movement. The knee joint angle is measured with an electric goniometer placed on the lateral side of the knee. Surface EMG records the activity of the m. Rectus femoris and the Semitendinosus muscles. Electrode placement, skin preparation and related issues are performed according to the guidelines presented by SENIAM (Hermens et al. 1999).

Table 1: Measurements to be performed

| Period                               | Measurement                                                                                                                                                                                                                                                    | Content                                                                                                                                                                                |                                               |
|--------------------------------------|----------------------------------------------------------------------------------------------------------------------------------------------------------------------------------------------------------------------------------------------------------------|----------------------------------------------------------------------------------------------------------------------------------------------------------------------------------------|-----------------------------------------------|
| T1                                   | Modified Nottingham Sensory Ass
Mini-Mental State Examination
Utrecht Communicatie Onderzoek                                                                                                                                                             | proprioception and sensation
cognition
communication                                                                                                                             | *
**
***                                |
| T1, T9, T17, T26, T52                | Clinical Gait analysis
Mappam test
Modified Ashworth Scale
Brunnstrom Fugl Meyer (leg portion)
Passive ankle range
Barthel Index
Nottingham Extended ADL (T26/52)
Stroke Impact Scale                                                     | joint angles/EMG/GRF
stretch reflex, instrumented
resistance to passive
motion
synergies
passive range of motion
ADL
extended ADL
quality of life after stroke | *
*
*
*
*
**
**
**       |
| T1-T18: 2-week interval,
T26, T52 | Motricity Index (leg portion)
10-m walking test
6-min walking test
Berg Balance Scale
Timed Up and Go test
Stairtest
Rivermead Mobility Index
Functional Ambulation Categories
therapist- and subject questionnaires
(attachment 1) | muscle control and strength
walking speed
walking endurance
balance
mobility
mobility
mobility
independence in walking
treatment and falls                     | *
*
*
*
*
*
**
***
** |
| T1-T26: every month,
T52          | Falls Efficacy Scale
subject questionnaire (attachment 2)                                                                                                                                                                                                   | fear of falling
pain and AFO/shoe use                                                                                                                                               | **
**                                      |

*T1 = week of inclusion and providing AFO to the “early” group;*

*T9 = week of providing AFO to the “late” group;*

*T26 = 6 months after stroke*

*T52 = 12 months after stroke*

*\*) physical test; \*\*) questionnaire; \*\*\*) rating scale*

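### The rule that every clinical test is done with AFO cannot be met by the late arm before week 9, and it leaves the main performance tests without a comparable baseline at T1

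*Protocol*

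**What the plan says.** Protocol section 6.3, under Clinical tests, sets one wearing condition for the whole battery: "All the clinical tests are performed with AFO". Table 1 schedules most of these tests from T1 at two-week intervals up to week 18, then at T26 and T52. No visit before T1 is listed.

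The Table 1 footnotes define the two key weeks: "T1 = week of inclusion and providing AFO to the" early group, and "T9 = week of providing AFO to the" late group. Section 3 says of the late arm: "In the period before receiving the AFO, this group will practise walking and transferring without support of the ankle and foot". Bandaging is permitted, but only within physiotherapy sessions.

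Gait analysis, in the same section 6.3, is handled differently. At T1 the subjects of the early group "receive their AFO at the beginning of this week and are measured with and without AFO", while the late "AFO group will be measured without AFO". From T9 both arms are measured both ways.

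Section 6.1.1 makes the activity-level clinical tests the main endpoints. Gait analysis serves the secondary objective on walking impairment (section 6.1.2). Section 8.2 plans a between-group comparison by t-test or a non-parametric equivalent. It names neither a change from T1 nor a baseline covariate.

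**The concern.** Two things follow from the section 6.3 sentence. First, the late arm cannot comply before week 9, so assessors have no valid instruction for half the trial at the early visits. Second, a test done with the AFO on can only take place once the AFO has been provided. In the early arm, the first recorded value of each performance test therefore already contains whatever wearing the device does at once. In the late arm it does not.

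The protocol provides a same-condition T1 measurement for the secondary gait outcomes but not for the main ones. At stake are the check of baseline balance on the main performance tests, the precision that a good baseline covariate would bring to a trial whose size was set by feasibility, and the meaning of any change from T1. A score that was never collected cannot be recovered by a statistical analysis plan.

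**Working it through.** **The passages side by side**

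| Visit | Early arm | Late arm | Can the section 6.3 rule be met? |
|---|---|---|---|
| T1 | AFO provided this week; clinical tests with AFO | no AFO | early arm only, after provision |
| T3, T5, T7 | with AFO | no AFO | early arm only |
| T9 | with AFO | AFO provided this week | both arms, if late-arm testing follows provision |
| after T9 | with AFO | with AFO | both arms |

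Counting in two-week steps from T1, four clinical-test visits fall before the late arm has an AFO. The protocol puts AFO provision before the T1 measurement explicitly only for gait analysis. The day of the T1 clinical tests is not given, but testing with the AFO on implies the same order.

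**The plan's own figure.** Section 4.4: 20 subjects per year × 30/12 years = 50, which reproduces. The protocol gives no effect size, SD or power.

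**Inputs assumed here.** 25 per arm; outcomes in SD units, scored so that higher is better; equal SDs at T1 and follow-up; two-sided alpha 0.05 (section 8.2 gives 0.05 without sidedness). Immediate device effect e = 0.2 to 0.5 SD. Correlation r of T1 with the later outcome = 0.5 to 0.7. The documents give neither e nor r.

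**Bias if T1 is used as the reference, both arms wearing the AFO at the later visit**

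- Change score: early (Y − B − e) against late (Y − B), where B is the score without AFO. The contrast is the true difference − e, so the bias is −0.2 to −0.5 SD.
- T1 as covariate: with equal SDs the slope is r, so the bias is −r × e. This gives 0.5 × 0.2 = 0.10 SD up to 0.7 × 0.5 = 0.35 SD, against early provision.
- Unadjusted comparison at that visit: T1 does not enter, so this bias is 0.

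**What a usable baseline is worth**

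- Detectable difference at 80% power, no covariate: √(2/25) × (1.960 + 0.842) = 0.2828 × 2.802 = 0.79 SD (normal approximation).
- With a comparable baseline as covariate: 0.79 × √(1 − r²), that is 0.69 SD at r = 0.5 and 0.57 SD at r = 0.7.

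**What a difference before T9 contains.** Suppose wearing the AFO has only an immediate effect e. The chance that one such visit is significant is Φ(e/0.2828 − 1.96) + Φ(−e/0.2828 − 1.96):

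| e (SD, assumed) | 0.2 | 0.3 | 0.5 | 0.8 |
|---|---|---|---|---|
| chance of significance | 0.11 | 0.19 | 0.42 | 0.81 |

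A significant early difference therefore does not by itself show an effect on recovery beyond the device.

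**The case against.** The sentence may be shorthand for testing with the AFO once it has been provided. Nobody can fit an orthosis that a subject does not have. The same sentence also covers passive ankle range and the ankle Modified Ashworth Scale, which a worn orthosis would obstruct. That is a fair account of the intent, but it cures only the late-arm contradiction. The early arm would still be tested at T1 with the device on.

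A reader might infer that the trial's comparison of early and late provision is itself biased. The documents do not support this. Section 8.2 names no T1-based analysis, and a randomised between-arm comparison needs no baseline to be unbiased.

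A reader might also infer that differences before T9 are artefacts to be set aside. Having the AFO against not yet having it is largely the randomised contrast. Section 1 (New research) lists independence reached sooner in rehabilitation as one hoped-for benefit, so these visits belong to the question.

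Finally, not all main endpoints are equally affected. The Nottingham Extended ADL is taken only at T26 and T52. The Rivermead and Barthel are coded as questionnaires and the FAC as a rating scale, so the wearing condition matters less for them. Gait analysis does give both arms a without-AFO measurement at T1, but for secondary outcomes and, in the early arm, after provision.

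**Conclusion.** The point holds for the five performance tests: 10MWT, 6MWT, TUG, Stairtest and BBS. As written, the rule contradicts the late arm's schedule at four visits and removes a comparable T1 value for these tests. That loss is certain if the rule is followed, and it cannot be repaired at analysis.

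The bias figures (0.2 to 0.5 SD for change scores, 0.10 to 0.35 SD for T1 adjustment) are conditional. They require someone to use T1 as a reference, and they rest on the assumed device effect and correlation. Set against a detectable difference of about 0.79 SD, they would matter if such an analysis were done. An unadjusted comparison at visits where both arms have the AFO is untouched.

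**What to change.** Reword section 6.3, Clinical tests, as follows.

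1. At T1 the performance tests are done without AFO in both arms. In the early arm they are done before the AFO is handed out, where the existing schedule allows. This is the baseline. State the order of testing and provision in that week, because a T1 test that follows some days of use is a weaker baseline.
2. Reconcile the sentence with the Gait analysis text, section 3 and Table 1 by giving the wearing condition by arm and visit. The early arm is tested with AFO from T3. The late arm is tested without AFO until it is provided in week 9, and with AFO thereafter. Passive ankle range and the ankle Modified Ashworth Scale are exempt.
3. Label between-arm differences before T9 as including the immediate effect of wearing the AFO, and keep them within the timing question.

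The cost is a few sentences and the early arm's with-AFO clinical score at T1. The timing of AFO provision, the visits and the tests do not change.

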#### Hypothesis:

Compared to late provision, early provision of AFOs is expected to diminish the number of falls and fall related events as AFOs are expected to improve safe ambulation and diminish fear to fall.

- What are the effects of timing of providing ankle-foot orthoses on quality of life in acute stroke patients in a rehabilitation setting?

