The occurrence of falls and all fall related events are measured using questionnaires for therapists and subjects (see attachment 1).

Quality of life:

- Stroke Impact Scale (SIS version 3.0): evaluates the effects of stroke in terms of function, activities and participation. Fifty-nine items are scored on a 5-point scale

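### After T18 the number of falls rests on two contacts, T26 and T52 (gaps of about 8 and 26 weeks), so late falls are likely to be under-counted

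*Protocol*

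**What the plan says.** Falls are a secondary outcome with their own hypothesis, and that hypothesis concerns a count. In section 2 of the Protocol, "early provision of AFOs is expected to diminish the number of falls and fall related events". Section 6.1.2 names the instrument: "The occurrence of falls and all fall related events are measured using questionnaires for therapists and subjects (see attachment 1". Section 6.1.3 also lists falling among the items taken from the attachment 1 forms.

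Table 1 (section 6.3, Clinical tests) puts "therapist- and subject questionnaires (attachment 1", with content given as treatment and falls, in the row headed "T1-T18: 2-week interval, T26, T52". The text above the table agrees: "During the first 18 weeks of the study most clinical tests will be repeated with 2-week intervals", with repeats at 6 and 12 months after stroke.

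A separate row, "T1-T26: every month, T52", holds the Falls Efficacy Scale (fear of falling) and the attachment 2 questionnaire (pain, shoe and AFO use). Neither is listed as counting falls. The Protocol describes no fall diary, calendar or telephone contact.

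**The concern.** A count of falls is only as complete as the questioning behind it. Up to T18 each form has to cover about 2 weeks. The T52 form follows the previous one by up to 26 weeks, an interval 13 times as long. There are two ways the unseen form could work, and both lose events:

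- If it asks about everything since the last form, subjects must recall falls and near-falls over as much as half a year. Events without injury are the easiest to forget.
- If it asks about a fixed recent period, most of the time after T18 is never asked about.

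The Protocol gives the lack of evidence on long-term effects as its reason for the study, and T26 to T52 is the long-term period. An apparent drop in the fall rate after T18 could come from sparser questioning alone. No later analysis can recover falls that were never recorded.

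**Working it through.** The Protocol gives no fall rate, recall period or falls power to reproduce, so the check is schedule arithmetic.

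**Inputs.** The last 2-weekly form is at T18 (Table 1), or T17 if visits start at T1 and step by 2. T26 has two definitions: "The fourth gait analysis will be performed in week 26 of the study, approximately 6 months after stroke" (section 6.3, Gait analysis) and "T26 = 6 months after stroke" (Table 1 footnote). T52 is 12 months after stroke. Inclusion is about 2 weeks after stroke in practice (section 3) and at most 6 weeks after (section 4.2).

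**Both labels in study weeks.**
- First gap: 26 − 18 = 8 weeks (26 − 17 = 9).
- Second gap: 52 − 26 = 26 weeks.
- Share of the year after the 2-weekly phase: (52 − 18)/52 = 34/52 = 65%. With T17 as last visit it is 35/52 = 67%. Counted from T1 it is 34/51 = 67% or 35/51 = 69%.

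**Both labels counted from stroke.** With inclusion in week s after stroke, study visit T falls in post-stroke week s + T − 1. The first gap is 26 − (s + T − 1), and the share is (52 − (s + T − 1))/(52 − s).

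| s | Last 2-weekly visit | Post-stroke week | First gap (weeks) | Second gap (weeks) | Share |
|---|---|---|---|---|---|
| 2 | T17 | 18 | 8 | 26 | 34/50 = 68% |
| 2 | T18 | 19 | 7 | 26 | 33/50 = 66% |
| 6 | T17 | 22 | 4 | 26 | 30/46 = 65% |
| 6 | T18 | 23 | 3 | 26 | 29/46 = 63% |

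**Mixed labels.** If T26 is taken as study week 26 but T52 as one year after stroke, the second gap is 52 − (s + 25) = 27 − s, which is 25 weeks for s = 2 and 21 weeks for s = 6. The first gap is then 8 or 9 weeks, and the shares in the table do not change.

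The share is thus 63% to 69% on every reading. The second gap is 26 weeks when both labels have the same origin and still at least 21 weeks when they do not.

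**Illustration of size (assumed inputs only).** Take a constant fall rate, full capture to T18, and capture a and b in the two gaps. The captured share of the year's falls is c = (18 + 8a + 26b)/52. If the counts were Poisson with the same c in both groups, the standard error of the log rate ratio would grow by 1/√c.

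| a | b | c | 1/√c |
|---|---|---|---|
| 0.9 | 0.8 | 46/52 = 88% | 1.06 |
| 0.8 | 0.6 | 40/52 = 77% | 1.14 |
| 0.7 | 0.5 | 36.6/52 = 70% | 1.19 |

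If the form asked only about the last 2 weeks, (18 + 2 + 2)/52 = 22/52 = 42% of the year would be observed.

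**Effect on the comparison.** With true mean counts E (early) and L (late) and equal capture c, the observed ratio is cE/cL = E/L, which is unchanged. The observed difference is c(L − E), which is smaller. Equal under-capture therefore shrinks a difference in mean counts and loses precision, but does not favour one group.

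**The case against.** The strongest reply is that attachment 1 is not shown. It might hold a running log, and its recall period is unknown. That limits how firmly the loss can be stated, so likely is the right word. It does not rescue the schedule, because a form given at these visits loses late events under either recall period.

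Second, falls can also be recorded as adverse events under section 7.2, so attachment 1 is not the sole route. That stands. But section 7.2 relies on what subjects volunteer or staff observe, so it would catch only some falls and few near-falls.

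Third, the groups differ in AFO provision between T1 and T9. That period and the weeks after late provision up to T18 fall within 2-weekly questioning, and both groups follow the same schedule afterwards. This stands and sets the scope of the point. A reader might infer that the late comparison is biased between groups, or that finding no late difference would be uninterpretable. The documents do not support either. Section 6.2 states that subjects and assessors are not blinded, so unequal recall cannot be excluded, but nothing in the Protocol indicates it.

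A reader might also tie the drop in questioning to discharge home, or discount the therapist as a source from then on. The Protocol gives no discharge timing. Section 4.2 also requires that subjects have no severe deficits in memory and understanding.

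Finally, this is one secondary outcome in an explorative study of about 50 subjects, and sparser late follow-up limits burden. That is a fair reason to keep the remedy light.

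**Conclusion.** The point holds as a weakness of data collection for a secondary outcome. About two thirds of the follow-up year (63% to 69%, depending on how the visit labels are read) rests on two fall contacts. The first gap is about 8 weeks, or 3 to 4 weeks for the latest entrants if T26 is counted from stroke. The second is 26 weeks, or 21 to 25 weeks if T26 and T52 have different origins. Falls after T18, especially events without injury, are likely to be under-counted.

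The direction follows from the schedule. The size does not, and the capture percentages in the working rest on assumed recall and a constant fall rate. The consequence is lost events and precision in the 6-month, 12-month and full-year falls comparisons. The comparison up to T18 is not affected. The change is worth making because the loss cannot be repaired afterwards and the remedy is cheap.

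**What to change.** In Table 1:

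1. **T18 to T26.** Add the fall items of attachment 1 to the monthly subject questionnaire (Falls Efficacy Scale and attachment 2), worded to cover the time since the previous form. This needs no new contact. It gives about one further fall count, near T21–T22, and so splits the 8-week gap roughly in half.
2. **T26 to T52.** Give subjects a one-page fall calendar, marked on the day of the event and returned monthly by post. Keep the T52 questionnaire as a back-up.

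The cost is a few added items up to T26. After that it is postage, reminders and data entry for up to 50 × 6 = 300 returns, a small added burden for subjects, and some calendars that will not come back. No extra visits are needed.
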